## Methods

The AURORA study is a prospective, multicenter, single-arm, cohort study that will be conducted in 14 high-volume centers with specified expertise in TAVR. Patients with symptomatic pure severe AR confirmed by an Echocardiographic Core Laboratory who are ≥ 65 years will be consecutively enrolled for multidetector computed tomography (MDCT) scanning. After discussions with the heart team, the patients who are considered to have a prohibitive or high risk for surgery will be classified into 4 types: types 1, 2 and 3 patients who have more than 2 anchoring areas for THV will be treated with the TAVR procedure, whereas patients classified as type 4 who have only 1 area [either at the left ventricular outflow tract (LVOT), annulus, or ascending aorta (AA)] or no suitable area for anchoring will continue to receive medical treatment. Procedural and 30-day, 3-month, 6-month and 12-month outcomes will be assessed according to the Valve Academic Research Consortium-3 consensus (VARC-3 criteria). Enrollment is expected to be completed within 18 months. Institutional ethical approval will be requested in each center according to local regulations that comply with the principles outlined in the Declaration of Helsinki for research in human subjects. The study flow chart is depicted in Fig. 2.

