### Study end points

The study end points will be defined according to VARC-3 criteria [15]. The primary efficacy end point is the device success rate. The second efficacy end point is the composite of technical success and improvement in AR severity after the procedure. Furthermore, we will investigate several additional secondary end points, including the rate of rehospitalization for heart failure, change in functional capacity as indicated by whether the patient is rated as the New York Heart Association functional class I or II, the 6-min walk distances, and the plasma concentration of N-terminal fragment brain natriuretic peptides (NT-proBNP) at 12 months compared with baseline. We will also assess myocardial remodeling by determining changes in the echocardiographic parameters of left ventricular remodeling at 12 months, as well as the quality of life utilizing the Kansas City Cardiomyopathy Questionnaire (KCCQ) score.

The safety end points include the major adverse cardiovascular and cerebrovascular events, which are defined as the composite end points of death, stroke, myocardial infarction, renal failure, arrhythmia, and conduction block occurring after the puncture, and reoperation for device- or procedure-related adverse events. All-cause mortality (30 days, 6 and 12 months after the procedure), cardiovascular mortality (30 days, 6 and 12 months after the procedure), and the post-procedure rehospitalization rate due to heart failure (30 days, 6 and 12 months after the procedure). All primary and secondary end points and the relationship of the event to the device and to the operation will be determined by an independent clinical event committee based on the prespecified definitions after review of the original medical documentation. The details of the study end points are summarized in Table 2. Details of the assessment performed during hospitalization and at each follow-up visit are depicted in Table 3. Follow-up visits are planned at 1 month, 6 months, and 12 months for all patients after discharge, irrespective of whether devices are implanted. Collection of routinely available clinical data will be discontinued only if explicitly request by the subject.

**Table 2 Tab2:** Study endpoints

*Primary efficacy endpoint*

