### Statistical analyses

Data will be expressed as mean ± standard deviation for continuous variables and compared using the unpaired Student *t*-test or the Mann–Whitney U test. Categorical variables will be reported as numbers with the relative percentage and compared using the χ^2^ or the Fisher exact test as appropriate.

A recent meta-analysis [1] has reported a device success rate of TAVR for AR of 80.4% (95% confidence interval, 72.2–88.6%). According to the results of our feasibility study using this novel anatomical classification and dual anchoring theory, the expected device success rate of this study is set at 90%. Consequently, a minimal number of 86 severe pure AR cases at high risk for surgery is needed to appropriately answer the primary objective of the study. Our goal is to recruit 100 patients to account for 10% missing data or loss of patients to follow-up. A p-value of < 0.05 will be considered significant. Statistical analyses will be performed using the SPSS software (version 24.0) (IBM Corp., Armonk, NY, USA).

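### The stated minimum of 86 cases cannot be reproduced from 80.4% versus 90% at a conventional power: an exact test on 86 has about 64% power two-sided or 76% one-sided

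*Protocol article*

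**What the plan says.** The Methods section describes a "prospective, multicenter, single-arm, cohort study". Under Study end points, "The primary efficacy end point is the device success rate", which Table 2 places at 30 days.

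The sample size is in the Statistical analyses section. It cites a meta-analysis with a device success rate of 80.4% (95% confidence interval 72.2 to 88.6%). It then says that, on the strength of a feasibility study, "the expected device success rate of this study is set at 90" per cent. As the consequence of these two rates, it concludes that "a minimal number of 86 severe pure AR cases at high risk for surgery is needed" for the primary objective. Recruitment is set higher: "Our goal is to recruit 100 patients to account for 10% missing data or loss of patients to follow-up".

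The only error threshold is the general sentence "A p-value of < 0.05 will be considered significant". No power, sidedness or null hypothesis appears. For categorical variables the section names the chi-square and Fisher exact tests, in a general sentence on comparing variables. Neither is linked to the 80.4% rate.

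**The concern.** The section presents 86 as the result of a derivation, so a reader should be able to get close to it from the rates and threshold given. With one arm and an external rate, the natural reading is a one-sample test of device success against 80.4%. On that reading 86 matches no usual combination of power and sidedness, and it gives less than 80% power on either side.

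The primary objective rests on this number. At two-sided 5%, the usual meaning of an unqualified p < 0.05, 86 patients would have to yield at least 77 successes (77/86 = 89.5%), almost the whole expected rate. Leaving the side open also leaves some results undecided: with 90 evaluable patients, 79 successes pass at one-sided 5% and fail at two-sided 5%.

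**Working it through.** **Inputs from the Statistical analyses section:** benchmark p0 = 0.804, expected rate p1 = 0.90, difference 0.096, alpha 0.05, stated minimum 86, target 100, loss 10%.

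**Assumptions of this check:** a one-sample test against p0; sidedness tried both ways; power of 80% as the convention, with 85% and 90% also tried. A two-sided 5% exact test is taken to require an upper tail of at most 2.5%.

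**Step 1. Attempt to reproduce 86.** The score formula is n = [z_a·√(p0(1−p0)) + z_b·√(p1(1−p1))]² / (p1−p0)², with √(0.804×0.196) = 0.3970 and √(0.9×0.1) = 0.3.

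- One-sided 5%, 80% power: [(1.645×0.3970 + 0.842×0.3)/0.096]² = 88.96, so 89.
- Two-sided 5%, 80% power: [(1.960×0.3970 + 0.842×0.3)/0.096]² = 115.2, so 116.
- 90% power: 117 one-sided, 147 two-sided.

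Other routes:

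- Arcsine formula, one-sided 5%, 80% power: 83.
- Score formula with the benchmark rounded to 0.80, one-sided 5%, 80% power: 83.
- Formula with the variance at p1 only (Wald), n = (z_a+z_b)²×0.09/0.096²: 84 (one-sided, 90% power) or 88 (two-sided, 85% power).

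Several routes come within a few patients and none gives 86. The Wald test is also not valid at this size. At n = 86 it would declare success from 75 (one-sided) or 76 (two-sided), with true upper-tail errors of 6.8% and 3.6% against nominal 5% and 2.5%.

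**Step 2. What 86 delivers.** Find the smallest r with P(X ≥ r | 86, 0.804) within the limit, then take P(X ≥ r | 86, 0.90).

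- Two-sided 5%: r = 77, upper tail 1.8%, power 64.3%.
- One-sided 5%: r = 76, upper tail 3.6%, power 76.1%.

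The score z-test has the same cut-offs at n = 86, so its actual power is the same. Its normal approximation gives 64.6% and 78.6%. The arcsine approximation gives 71.9% and 81.4%.

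**Step 3. Exact sample size.** The first n with exact power of at least 80% is 90 one-sided and 109 two-sided.

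**Step 4. The recruitment target.** 86/0.9 = 95.6, so 96; a target of 100 covers the stated loss. Conversely 100 × 0.9 = 90. Exact power at and around 90:

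| Evaluable n | One-sided 5%: successes needed, power | Two-sided 5%: successes needed, power |
|---|---|---|
| 86 | 76, 76.1% | 77, 64.3% |
| 90 | 79, 81.4% | 80, 71.3% |
| 92 | 81, 79.3% | 82, 68.7% |
| 95 | 84, 76.1% | 85, 64.9% |
| 100 | 88, 80.2% | 89, 70.3% |

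Power does not rise steadily with n, because the cut-off moves in whole patients.

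**The case against.** The strongest reply is that nothing stated is contradicted. No power is declared, the p < 0.05 sentence is general and not attached to the sample size, and a journal article may leave the test and its side to the full protocol or analysis plan. This stands in part. A reader might infer that 86 is an outright arithmetic error, or that it must come from an invalid method. The documents support neither: without a declared power 86 cannot be proved wrong, and legitimate approximations at one-sided 5% and 80% power give 83 and 89, on either side of it. What survives is that the article itself presents 86 as the consequence of two rates, and those rates do not yield it under a standard valid test at a conventional power.

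Second, the one-sided shortfall is slight: 1.4 points below 80% by the normal approximation (80 − 78.6) and 3.9 by the exact test (80 − 76.1). The exact power at 86 equals that at 95, so part of the gap is discreteness. This stands. It does not rescue the two-sided reading.

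Third, the trial recruits 100, not 86. A reader might infer that a truly 90% strategy would be missed about one time in three. That figure (100 − 64.3 = 35.7%) needs exactly 86 analysed patients and a two-sided test. At 90 evaluable the risk is 28.7% two-sided and 18.6% one-sided.

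Fourth, chi-square can be run as a one-sample test, so it is too strong to say that the named tests exclude the right analysis. The text only leaves the benchmark comparison without an identified test.

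**Conclusion.** The point holds in a limited form and should be fixed. From 80.4% versus 90% with p < 0.05, the minimum of 86 is not reproducible at a conventional power with a standard valid one-sample test. Exact power at 86 is about 64% two-sided or 76% one-sided. Reaching 80% takes 116 by the score formula (109 is the first exact n) two-sided, or 89 (90 is the first exact n) one-sided. The two-sided shortfall is material and the one-sided shortfall is small.

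This rests on treating 80.4% as a fixed null value, which the article implies but does not write, and on 80% as the conventional power. It does not show that the study needs more patients. The recruitment target can support about 80% power on a one-sided reading, provided that enough of the 100 are treated. The article says only that 100 will be recruited, while type 4 patients receive medical treatment and follow-up covers patients with and without a device. Ninety evaluable treated patients is therefore an assumption.

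**What to change.** Restate the sample size paragraph and leave recruitment unchanged.

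- Replace 86 with the evaluable number that the target supports: 90, if all 100 are TAVR-treated and 10% are lost. State that assumption, and say whether type 4 patients count towards the 100.
- Name the primary analysis: an exact one-sample binomial test of device success against 80.4%, with a Clopper-Pearson interval at the level that matches the chosen side.
- Fix the side before outcome data are seen and give the threshold and true power: at least 79/90 with 81% power at one-sided 5%, or at least 80/90 with 71% power at two-sided 5%.
- Add that exact power moves with the final number analysed, for example 76% one-sided at 95 and 80% at 100, and that the cut-off will be recalculated for that number.

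The cost is wording only. The one drawback is that the stated power may look less favourable, above all if the two-sided test is chosen.

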## Discussion

To the best of our knowledge, this is the first prospective, multicenter cohort study to evaluate the safety and efficacy of TAVR for pure severe AR in a large sample of high-risk surgical patients. Moreover, our study will be the first to systematically analyze the anatomical characteristics of the aortic root in patients with pure native AR by MDCT multiplanar measurements. Based on this approach, we will propose a new anatomical classification and develop a novel dual anchoring theory with specific releasing strategies to improve the device success rate in TAVR, which will lead to significant breakthroughs in screening suitable patients for TAVR and improving the prognosis of patients with AR with a high risk for surgery.

Many existing studies have described the anatomical characteristics of the aortic root in patients with AS to guide the TAVR procedure [16]. However, a systematic analysis of aortic root anatomy in patients with AR is rare. Modern MDCT imaging approaches have the potential to accurately analyze the morphological characteristics of the aortic root in patients with AR, expanding from the LVOT to the AA, which may provide precise guidance for TAVR in high-risk surgical patients. Based on multiplanar analyses of aortic root morphology in patients with AR, we found that the THVs can be anchored not only in the annulus but also in other zones of the pathway from the LVOT to the AA. Dual anchoring areas will significantly improve the stability of the device in patients with pure AR. Therefore, we have developed a novel AR imaging classification to divide patients with AR into 4 types according to the anchoring levels. In patients with a type 1 anchoring level, THVs anchored from the LVOT–annulus area to the AA are the most stable. In type-2 patients, although the LVOT–annulus area is significantly dilated, the AA can provide a good anchoring level to improve device stability. In type-3 patients, the STJ and AA are severely dilated, and the LVOT–annulus levels play a major role in anchoring the THV, which may be more likely to result in the malposition of the THV.

Due to the significant differences in aortic root anatomy among the 3 types, we recommend different strategies for selecting the valve oversizing index and for deploying the valve. In patients with type 2, the THV should be released as rapidly as possible under rapid pacing (180 beats/min) until the AA anchoring works. For patients with types 1 and 3, we recommend deploying the THVs at the LVOT–annulus area in 2 stages as described previously. In these latter types, it is essential to ensure adequate anchoring without any significant perivalvular leakage before complete deployment.

In addition, we cannot ignore the fact that the large oversizing index may lead to compression of the conduction system by the valve frame and an increased risk of the need to implant a new pacemaker. In this study, we will use the VitaFlow device because this THV has a straight cylindrical shape with an outer skirt that may lead to increased friction between the prosthesis and the surrounding tissues and may help avoid displacement of the device. We speculate that the second-generation device with a recyclable system can be used in the higher releasing position to reduce the occurrence of abnormalities of the conduction system. However, the key breakthrough of TAVR for patients with AR is to design suitable devices based on the morphological classification and the dual anchoring theory.

## Data Availability

The datasets used and/or analyzed during the current study are available from the corresponding author on reasonable request.

## Abbreviations

AURORA: Anatomical classification and dUal anchoRing theory to Optimize the tavR strategy for pure severe Aortic regurgitation
TAVR: Transcatheter Aortic Valve Replacement
AS: Aortic Stenosis
AR: Aortic Regurgitation
THV: Transcatheter Heart Valve
MDCT: MultiDetector Computed Tomography
LVOT: Left Ventricular Outflow Tract
AA: Ascending Aorta
VARC-3: Valve Academic Research Consortium-3 consensus
LCC: Left Coronary Cusp
NCC: Non-Coronary Cusp
RCC: Right Coronary Cusp
STJ: SinoTubular Junction
NT-proBNP: N-terminal fragment Brain Natriuretic Peptides
KCCQ: Kansas City Cardiomyopathy Questionnaire
